### Sample size and data analysis

No prospective data are available regarding haemodynamic predictors of aneurysm recurrence after endovascular treatment. According to our previous retrospective study,^14^
^25^ the recurrence rate of aneurysms was approximately 10%. A mean reduction in flow velocity of 20%±10% was associated with recurrence, and a reduction of 30%±15% was associated with stability. A sample size of 150 patients will be included with a two-sided significance level of 5% and a power of 80%. The rate of included patients that will be lost to follow-up is assumed to be 10%, and a sample size of 167 patients will be needed. Finally, a total of 200 patients will be enrolled.

Data will be presented as mean and SD for quantitative variables or frequency for qualitative variables. Analysis of factors affecting angiographic and clinical outcomes will be performed. Potential associations between patients, aneurysms, procedural characteristics, or haemodynamic parameters and outcomes will be assessed by univariate analysis using the Student's *t*-test, the Wilcoxon test, the χ^2^ test, or Fisher's exact test, as appropriate, and by multivariate analysis. Logistic regression will include all variables with p<0.20 by univariate analysis. Statistical significance will be recognised when p<0.05. Statistical analysis will be performed using IBM SPSS Statistics for Windows, V.21.0 (IBM Corp, Armonk, New York, USA).

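### Naming Welch's t-test in place of Student's for the recurrence comparisons would restore the nominal error rate and add about 10 to 14 points of power, with no added patients

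*Protocol article*

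**What the plan says.** All of this stands in the Protocol article under Sample size and data analysis.

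- Event rate, from earlier retrospective work: "the recurrence rate of aneurysms was approximately 10" per cent.
- Planning effect: "A mean reduction in flow velocity of 20%±10% was associated with recurrence, and a reduction of 30%±15% was associated with stability".
- Size: "A sample size of 150 patients will be included with a two-sided significance level of 5% and a power of 80" per cent.
- Attrition: "lost to follow-up is assumed to be 10%, and a sample size of 167 patients will be needed".
- Enrolment: "Finally, a total of 200 patients will be enrolled".
- Analysis: associations with outcome "will be assessed by univariate analysis using the Student's" t-test, the Wilcoxon test, the χ² test or Fisher's exact test, as appropriate. Variables with p<0.20 then enter a logistic regression, and significance is declared at p<0.05.

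The section gives no sample-size formula and does not tie the 150 to a particular test. It names no unequal-variance t-test.

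**The concern.** Student's t-test pools the two variances, weighting each by its degrees of freedom. When one group is about nine times the other, the pooled variance is nearly that of the large group. Here the large (stable) group is assumed to be the more variable one, so its variance is applied to the small recurrence group, which dominates the standard error. The standard error comes out too large, p-values too high and confidence intervals too wide.

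What is at stake is sensitivity. The study exists to identify haemodynamic factors linked to recanalisation, and the univariate test decides which variables reach the logistic regression. The section Computational fluid dynamics simulations and haemodynamic analysis lists wall shear stress, velocity and pressure, averaged and maximum, at two regions, compared as reduction ratios. A parameter with a similar variance pattern but a smaller effect than the planning one could be screened out because of the test used.

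**Working it through.** **Inputs.** From Sample size and data analysis: means 20 and 30 (difference 10), SDs 10 and 15, recurrence 10%, two-sided 5%, power 80%, 150 evaluable, 10% loss, 200 enrolled. Assumptions: ± is an SD (the section presents data as mean and SD), data are normal, and the split is exactly 10:90. That gives 15 v 135 at 150 evaluable. For 200 enrolled, 200 × 0.90 = 180 evaluable, or 18 v 162.

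**1. Reproducing the plan's 150.** Average the two variances equally: (10² + 15²)/2 = 162.5, SD 12.75. With a 1:9 ratio,

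n₁ = (1.960 + 0.842)² × 162.5 × (1 + 1/9) / 10² = 7.849 × 162.5 × 1.111 / 100 = 14.17.

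Rounded up this is 15 recurrent, with 9 × 15 = 135 stable, total 150. Nominal power at 15 v 135 with that SD is 82%. Then 150/0.90 = 167. Both stated figures are recovered.

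**2. Does that averaging suit the tests?** At 1:9 it matches neither.

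- Student's test uses a degrees-of-freedom weighting: (14 × 100 + 134 × 225)/148 = 213.2, SD 14.6, not 12.75.
- The unequal-variance normal formula gives n₁ = 7.849 × (100 + 225/9)/100 = 9.81, or about 100 in total.

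**3. Standard errors at 15 v 135.**

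- Pooled: 14.6 × √(1/15 + 1/135) = 3.97.
- Actual: √(100/15 + 225/135) = 2.89.
- Ratio: 3.97/2.89 = 1.38 (to two decimals), so the pooled value is about 38% too large.

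**4. Simulated operating characteristics at p<0.05** (normal data, SD 10 v 15, 1,000,000 runs).

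| Split | Test | Type I error | Power, difference 10 |
|---|---|---|---|
| 15 v 135 | Student | 0.73% | 77.1% |
| 15 v 135 | Welch | 5.0% | 91.1% |
| 18 v 162 | Student | 0.74% | 85.8% |
| 18 v 162 | Welch | 5.1% | 95.4% |

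The gain from Welch is 91.1 − 77.1 = 14.0 points at 150 evaluable and 95.4 − 85.8 = 9.6 points at 180. Student's test reaches 80% at about 160 evaluable (16 v 144).

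If the number of recurrences varies binomially, power at 150 is 74.4% (Student) and 88.6% (Welch). At 180 it is 83.4% and 93.7%.

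**5. The p<0.20 screen at 18 v 162.**

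| True difference | Student passes | Welch passes |
|---|---|---|
| 0 | 8% | 20% |
| 5 points | 55% | 72% |
| 10 points (planning effect) | 98% | 99% |

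For the 5-point difference, power at p<0.05 is 21% with Student and 45% with Welch.

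**6. The other listed test.** At 15 v 135 the Wilcoxon test has about 83% power and rejects about 1.7% of the time when the means are equal (20,000 runs).

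**The case against.** The strongest reply has four parts.

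*The plan leaves room.* It says the tests are chosen as appropriate, does not state equal variances, and names SPSS, which prints an unequal-variance row beside the pooled one. An analyst who let Levene's test choose the row would have about 84.9% power and 3.8% type I error at 150 evaluable (91.8% and 4.0% at 180). This stands in part: the 0.7% figure belongs to the pooled test, not to every possible reading. But the protocol states no such rule, and the choice it does offer is among the listed tests. Neither listed test for quantitative data is built for unequal variances. At 15 v 135 Levene's test detects this inequality only about 40% of the time, so it is a weak guide.

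*The sample size.* A reader might infer that 150 is a miscalculation. The documents do not support that: it follows from the stated inputs with the two variances averaged equally. A reader might also infer that the study is underpowered. At 150 the pooled test falls about 3 points short of 80%, but 200 will be enrolled, and about 180 evaluable patients give about 86% even with Student's test.

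*The direction of error.* A true rate of 0.7% means fewer false positives, not more. That stands; the cost is lost power.

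*The planning effect passes the screen anyway.* This is also true, at about 95% or more with either test. The loss falls on smaller effects, as the 5-point row shows.

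**Conclusion.** The concern holds as a point about test choice. On the plan's own inputs Student's test runs at about 0.7% instead of 5%, and passes about 8% of null variables through a 20% screen. It gives up about 14 points of power at 150 evaluable and about 10 at 180 compared with Welch. Enrolling 200 restores the power for the planning effect but not the calibration: the type I error is the same at 18 v 162. The equal averaging behind the 150 is a modelling choice that fits neither test at a 1:9 split; it is not an error of arithmetic.

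The figures depend on ± being an SD, on normal data, on a split near 10:90, and on the smaller SD lying in the recurrence group. The inputs come from retrospective work, a type of study that the Introduction describes as small in sample size, so the exact values are approximate. If the SDs prove equal, the pooled test is correctly calibrated and Welch costs some power: at a common SD of 15 and 18 v 162, 76% for Student against 73% for Welch. That is a small price beside the gain under the SDs that the plan itself assumes.

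**What to change.** In Sample size and data analysis, name Welch's unequal-variance t-test, with its confidence interval, for all quantitative comparisons of recurrence against no recurrence, including the p<0.20 screen. Fix this in advance and do not let a preliminary variance test decide. Restate the power for that test, with the inputs and the 1:9 split written out: about 91% at 150 evaluable (15 v 135) and about 95% at 180 (18 v 162).

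The cost is one sentence on the test and a line of restated power. The software already named prints the Welch result. No change in enrolment or data collection is needed.

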### Geometric reconstruction and modelling techniques

All pre-embolised and post-embolised 3D aneurysm geometries will be obtained from digital subtraction angiography images.^7^
^8^
^14^ We will first segment and surface-smooth the images using Geomagic Studio, V.12.0 (Geomagic, Research Triangle Park, North Carolina, USA) and save the surface geometries in standard tessellation language format. As described in a previous study, the entire aneurysm model will be accurately and consistently separated into two regions: the aneurysm dome region that is embolised with coils, and the residual neck and parent vessel region.^14^

The porous media method will be used for intra-aneurysm coil modelling in the aneurysm dome region.^14^
^19^ Briefly, the aneurysm dome will be filled with porous medium corresponding to the coil mass, and the remaining vessel volume will be filled with fluid as blood flow. Packing density is defined as the ratio between the volume of the coils and the volume of the aneurysms. The parameter settings for coil modelling will be calculated based on the packing density.^14^
^19^
^20^

If a stent is used in clinical treatment, a novel virtual stenting workflow will be used to model intracranial stent deployment.^14^
^20^
^21^ Briefly, the workflow consists of three steps. (1) Pre-processing isolates the parent vessel and generates a simplex mesh structure along the vessel centre line. (2) Simplex mesh expansion occurs when the simplex mesh radially expands using mathematical forces. When the deployed simplex mesh has good apposition with the parent vessel wall, the deployment stops. (3) Post-processing maps and sweeps the stent into the final structures according to the types of devices. Finally, the post-embolised aneurysm model will be created using a porous media method and virtual stenting technique appropriately.

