We will then post-process and visualise the results of these simulations with the ANSYS CFD-Post. Haemodynamic parameters will be carefully examined at two regions: the aneurysm neck plane and the aneurysm dome. These parameters are wall shear stress, velocity, and pressure. The averaged and maximum values will be recorded. In addition to quantitative parameters, the qualitative parameter as inflow concentration will also be recorded. As described by Dhar *et al*,^24^ with estimation using multiple views of aneurysm geometries, the IA neck plane will be defined and created as the location from where the aneurysm sac pouches outward from the parent artery. Because flow in aneurysms before and after embolisation is different in each case, we will use the reduction ratio, which is calculated as: (parameter_pre_−parameter_post_)/parameter_pre_. This is a normalised parameter to allow comparison among different patients.^14^

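### The p<0.20 entry rule puts about 7 to 16 overlapping terms on 15 to 18 expected recurrences, so the multivariable step cannot reliably identify independent haemodynamic predictors

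*Protocol article*

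**What the plan says.** All references are to the Protocol article.

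- **Entry rule** (Sample size and data analysis): "Logistic regression will include all variables with p<0.20 by univariate analysis". No maximum number of terms, penalisation or choice among overlapping parameters is given. Significance is set at p<0.05.
- **Sample size** (same section): "the recurrence rate of aneurysms was approximately 10" per cent, and "A mean reduction in flow velocity of 20%±10% was associated with recurrence, and a reduction of 30%±15% was associated with stability". From these, "A sample size of 150 patients will be included", with a "two-sided significance level of 5% and a power of 80" per cent. Then "lost to follow-up is assumed to be 10%, and a sample size of 167 patients will be needed", and enrolment is set at 200.
- **Candidates**: Data collection and analysis lists the patient, aneurysm and treatment variables. The haemodynamic part of Computational fluid dynamics simulations and haemodynamic analysis names wall shear stress, velocity and pressure at the neck plane and the dome, and adds: "The averaged and maximum values will be recorded". Inflow concentration is recorded as well.
- **Simulation inputs** (Geometric reconstruction and modelling techniques): "The parameter settings for coil modelling will be calculated based on the packing density". Stents are modelled directly. Packing density and treatment technique are also candidate predictors.

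**The concern.** The study aims to find which haemodynamic factors affect recanalisation. The Introduction and Discussion already name aneurysm size, wide neck and incomplete initial embolisation as risk factors. The multivariable model is therefore the step that must separate haemodynamics from these.

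The rule lets the number of terms grow with the list of candidates, while the number of recurrences is small and roughly fixed. Overlap is built in: mean and maximum of one quantity come from the same flow field, and the simulation outputs depend on packing density and device, which may enter beside them. Correlated variables that pass the screen on their marginal association can then absorb a true velocity effect. Sparse data also push null terms below p=0.05 too often. The study could miss the effect on which it was sized and report another variable as an independent predictor.

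**Working it through.** **1. The plan's sample size.** Difference 30−20 = 10 points; SD = √((10²+15²)/2) = √162.5 = 12.75; allocation 1:9 from 10% recurrence.

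Recurrence group: (1+1/9) × 12.75² × (1.96+0.842)² / 10² = 14.17, rounded up to 15. With 135 stable, the total is 150, as stated. 150/0.9 = 166.7, so 167, as stated. The 80% is therefore reproduced by an unadjusted two-group comparison of one parameter.

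**2. Expected recurrences.** 150 × 0.10 = 15. With all 200 enrolled: 200 × 0.9 = 180, and 180 × 0.10 = 18.

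**3. Candidates.**
- Patient, 10: age, sex, smoking, alcohol, cholesterol, triglycerides, diabetes, hypertension, coronary disease, family history.
- Aneurysm, 9: size, neck, dome-to-neck ratio, dome-to-artery ratio, shape, location, presentation, rupture status, number.
- Treatment, 4: technique, number of devices, packing density, angiographic result.
- Haemodynamic, 13: 3 parameters × 2 regions × 2 summaries = 12, plus inflow concentration.

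The total is 36, before multi-level factors are coded as several terms.

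**4. Terms entering and events per term.** If nothing is related to recurrence, 36 × 0.20 = 7.2 terms enter, giving 15/7.2 = 2.1 to 18/7.2 = 2.5 events per term. With correlations of 0.5 to 0.85 between velocity and the other haemodynamic parameters, simulation admits about 11 to 16 terms. That gives 18/11 = 1.6 down to 15/16 = 0.9.

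**5. Variance inflation alone.** Power = Φ(10√(1−R²) / (12.75√(1/n₁+1/n₀)) − 1.96), where R² is the share of velocity explained by the other terms.

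| R² | 15 v 135 | 18 v 162 | N to keep the stated power, 150/(1−R²) |
|---|---|---|---|
| 0 | 82% | 88% | 150 |
| 0.25 | 70% | 78% | 200 |
| 0.5 | 53% | 61% | 300 |
| 0.8 | 25% | 29% | 750 |

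With 12 other parameters and a common correlation r, R² = 12r²/(1+11r). This is 1.08/4.3 = 0.25 at r = 0.3 and 3/6.5 = 0.46 at r = 0.5. The simulated losses below are larger, because sparse data and further terms add to the inflation.

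**6. Simulation of the screened model under the plan's velocity effect.** All haemodynamic parameters have equal pairwise correlation, and the others have no effect beyond velocity. Two sets were run. The second used 35 candidates (no inflow concentration), 500 runs per setting, and either no or four true clinical factors of 0.5 SD.

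| Correlation | Set 1, 15–18 events | Set 2, 15 events | Set 2, 18 events |
|---|---|---|---|
| 0 | 68–79% | 63–70% | 74–80% |
| 0.3 | 40–49% | 36–48% | 54–61% |
| 0.5 | 14–34% (over 0.5–0.85) | 25–33% | 32–43% |
| 0.7 | as above | 14–19% | 24–31% |

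In set 2, likelihood-ratio tests were only 2 to 6 points better than Wald tests, and separation or non-convergence occurred in about 1–16% of runs.

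**7. Spurious predictors.** At least one variable with no independent effect reached p<0.05 in about 70–80% of simulated studies in set 1 and 53–76% in set 2. In set 2, each such retained variable did so in 10–23% of cases instead of 5%. For comparison, 36 independent null tests at 5% with no model give 1 − 0.95³⁶ = 84%.

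**8. Small fixed model.** Velocity plus two covariates unrelated to it keeps about 73–87% power. If covariates explain 25% of velocity, step 5 gives 70–78%; if 50%, 53–61%.

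**The case against.** - **The stated power is not lost.** A reader might infer that the rule destroys the 80% in the sample size section. The document does not support this: the 80% belongs to the unadjusted comparison, which the plan includes and which keeps 82–88% by formula. Nowhere is 80% claimed for the multivariable model.
- **The model is not useless in every case.** A reader might infer that it cannot identify any predictor, or that power for velocity is only a few per cent. Values of about 2–8% arise only if the other 12 parameters are tied to velocity and otherwise mutually independent. That fits poorly with averages and maxima of the same fields. The documents give no correlations; at zero correlation power is still 68–79%, though zero is implausible here.
- **Multiplicity explains much of the false-positive figure.** This stands. Testing 12 further parameters one at a time, uncorrected, would still give 1 − 0.95¹² = 46% if they were independent.
- **A fixed model is not immune.** This also stands: its power falls if the chosen covariates explain much of velocity, and a three-class occlusion grade would add a term.
- **The article names no single primary model, and this is a registry that does not alter treatment.** True. The univariate results will also be reported, which limits the harm but does not make the adjusted results dependable.
- **An unseen analysis plan could hold collinearity checks.** It could, but the entry rule is stated outright here, so it is not a detail left open.

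**Conclusion.** The point holds in this form: the stated rule yields about 1 to 2.5 events per term, and the multivariable step cannot reliably identify independent haemodynamic predictors. The event counts and the 7 terms under no association follow from the document's own figures. The 11 to 16 terms, and power of 40–49% at correlation 0.3 and 14–34% at 0.5 to 0.85, rest on an assumed equal correlation among parameters. Other correlation structures can give lower power. The high chance of a spurious predictor does not need correlated parameters, but it comes partly from uncorrected multiplicity and not from the rule alone. The unadjusted velocity comparison remains adequately powered.

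**What to change.** Replace the p<0.20 rule with one pre-specified primary model: recurrence on the mean flow-velocity reduction ratio plus at most two single-term covariates that the article names as risk factors and already collects. Aneurysm size, and initial occlusion coded as complete versus not complete, are examples. Firth-penalised estimation is preferable at 15 to 18 events.

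In addition:
- Report each other haemodynamic parameter one at a time in the same fixed model, labelled exploratory or corrected for multiplicity.
- Do not enter the average and maximum of one quantity together.
- Fit packing density and device type, which feed the simulation, in a separate secondary model.
- State that the 80% power refers to the unadjusted velocity comparison.

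The cost is analysis wording only; no further patients or data are needed. The downsides are that not every recorded factor is adjusted for in one model, and that Firth estimation may need software beyond the SPSS version named.

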**Methods and analysis:**

This is a prospective, observational, registry study for patients with intracranial aneurysms who are treated endovascularly. It will enrol 200 eligible patients. Data on morphological, haemodynamic, and treatment factors will be collected prospectively. The advanced virtual stenting technique and porous media method will be used in haemodynamic simulations. The clinical and angiographic outcomes at 6 months will be measured and analysed. This observational study will determine the haemodynamic factors that affect the recanalisation of aneurysms.

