## Introduction

Due to its rapid development, endovascular treatment has become the first-line therapy for intracranial aneurysms (IAs).^1–3^ Endovascular treatment is associated with less invasiveness and lower morbidity compared with microsurgical clipping.^4^ However, recanalisation of aneurysms is a disadvantage of such a modality.^5–9^ Many factors, including complete initial embolisation, stent-assisted coiling, dense packing, and flow diverters, can reduce the recanalisation rate.^10–13^ The large size of aneurysm, wide neck, rupture status, and intraluminal thrombosis are risk factors of recanalisation of aneurysms.^6^
^9^ However, the haemodynamic mechanism has not been well studied and only a few studies have reviewed the relationship between haemodynamics and recanalisation of aneurysms. More importantly, no prospective cohort has analysed the haemodynamic risk factors affecting recanalisation of aneurysms and no high-level evidence has been obtained.

Haemodynamics play an important role in the initiation, growth and rupture of aneurysms.^7^
^8^
^14–16^ Previous studies have shown that haemodynamics are associated with outcomes of aneurysms after endovascular treatment. Studies have also shown that high wall shear stress and flow velocity are risk factors of recanalisation of aneurysms.^7^
^8^
^14^ However, these reports were retrospective studies with a small sample size, and no stent or flow diverter cases were involved. Outcomes of aneurysms after stent or flow diverter treatment via a haemodynamic method need to be prospectively analysed. As a future tool, simulations before the procedure may provide an optimal endovascular strategy to reduce the recanalisation rate at follow-up. Therefore, examining the haemodynamic predictors of recanalisation of aneurysms would of great value for clinical practice. In this observational study, we hypothesise that the haemodynamic mechanism plays an important role in the recanalisation of aneurysms after endovascular treatment. Additionally, the identified adverse haemodynamic factors could indicate a negative outcome of recanalisation.

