### Data collection and analysis

Data on patients, aneurysms, and treatment characteristics will be collected and recorded. The patient characteristics that will be recorded are age, sex, history of cigarette smoking and alcohol drinking, cholesterol/triglyceride values, any history of diabetes mellitus, hypertension, and coronary artery disease, and familial history of aneurysms. Characteristics of aneurysms that will be recorded are size, neck size, dome-to-neck ratio, dome-to-artery ratio, shape, location, clinical presentation, whether the aneurysm is ruptured or unruptured, and the number of aneurysms. Treatment-related factors will include treatment techniques, including coiling alone, balloon assistance, stent placement, or flow diverter treatment, the number of devices, packing density, and angiographic results.

Perioperative complications will be recorded and analysed. Immediate postoperative angiographic results and 6-month postoperative angiographic results will be collected. An independent angiographic committee will evaluate postoperative and 6-month occlusion of aneurysms, as well as the progress of occlusion of aneurysms. Occlusion of aneurysms will be evaluated using classification as complete occlusion, residual neck and residual aneurysm.^17^
^18^ Complete occlusion is defined as cases without any contrast media filling into the neck or sac of the aneurysm. The residual neck is defined as the existence of contrast media filling into the neck of the aneurysm on any single view projection, but without filling into the aneurysm sac. Any filling of the sac is classified as a residual aneurysm. Complete occlusion and a residual neck will be considered a satisfactory result, whereas a residual sac will be considered unsatisfactory. Progress of occlusion will be evaluated by direct comparison immediately after the operation with occlusion at 6 months, and described as one of three classes: improved, stable, or worse. Recurrence of aneurysms will be defined as any increase in contrast filling of aneurysms during follow-up.^18^ Angiographic follow-up will be routinely performed at 6 months after treatment. Clinical follow-up results will be analysed and recorded during hospitalisation for angiographic follow-up or by telephone interview using the modified Rankin scale score at 6 months. A modified Rankin scale score of 0–2 is a favourable outcome, and a score of 3–6 is an unfavourable outcome.

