## Discussion

Recanalisation of IAs following endovascular treatment is a major issue.^5–9^
^14^ Many factors, including incomplete initial embolisation, larger aneurysm size and wide neck, are considered to be associated with recanalisation.^6^
^9^
^18^ Use of stent-assisted coiling and flow diverters results in a lower recanalisation rate and higher complete occlusion rate.^26^
^27^ However, the underlying haemodynamic mechanisms are not totally understood.

In some retrospective studies, haemodynamics had a significant effect on recanalisation of an aneurysm following endovascular treatment.^7^
^8^
^14^ However, results from small retrospective cohorts were inconclusive, and a large, prospective study is needed. Our study is the first large, prospective study of haemodynamic factors in recanalisation of aneurysms after endovascular treatment. In this study, a novel patient-specific virtual stenting workflow, which more accurately reflects actual stent deployment, will be used to perform in vivo stent deployment for patients treated with stent-assisted coiling and flow diverters. Simulations with porous media for coil masses will be used in the present study. Such a method may reflect the real situation more accurately, creating more valid results.

With use of advanced techniques and a prospective design, this study may provide helpful information for improving the outcome of intracranial aneurysms in clinical practice. Results from this study may provide a chance to eliminate adverse haemodynamic factors before endovascular treatment or the patient may receive a more beneficial treatment strategy under haemodynamic analysis.

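### The p<0.20 univariate screen also applies to the haemodynamic parameters, so the study's own exposure can be dropped before its adjusted effect is tested if confounding masks the crude association

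*Protocol article*

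**What the plan says.** The Abstract gives the aim: "This observational study will determine the haemodynamic factors that affect the recanalisation of aneurysms". The Introduction gives the hypothesis: "we hypothesise that the haemodynamic mechanism plays an important role in the recanalisation of aneurysms after endovascular treatment". Haemodynamic parameters are therefore the exposure of interest, and patient, aneurysm and procedural factors are the background against which they are judged.

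The analysis text does not keep that distinction. Under Sample size and data analysis, "Potential associations between patients, aneurysms, procedural characteristics, or haemodynamic parameters and outcomes will be assessed by univariate analysis", followed by multivariate analysis, for which "Logistic regression will include all variables with p<0.20 by univariate analysis". No variable is exempt from the screen.

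The Introduction also names prognostic factors: "The large size of aneurysm, wide neck, rupture status, and intraluminal thrombosis are risk factors of recanalisation of aneurysms". The Discussion adds: "Use of stent-assisted coiling and flow diverters results in a lower recanalisation rate and higher complete occlusion rate". Size and neck are collected (Data collection and analysis: "Characteristics of aneurysms that will be recorded are size, neck size, dome-to-neck ratio, dome-to-artery ratio, shape, location"), so adjustment for them is possible.

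**The concern.** In an observational study the crude association of an exposure with outcome can be weaker than the adjusted one. Treatment here is not randomised. Suppose aneurysms at higher baseline risk (large, wide-necked) also had the greater simulated flow reduction, for instance because they more often received flow-reducing devices. The risk from size would then offset the benefit of flow reduction in the crude comparison. The parameter could miss p<0.20 and be left out of the only model able to separate the two effects.

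What is at stake is a false negative on the study's own hypothesis: a parameter would be set aside on a crude test, and its adjusted effect never estimated. This is a stated rule, so an analysis plan that followed it would inherit the problem.

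**Working it through.** **Inputs from the protocol article (Sample size and data analysis).** Recurrence is about 10%. Velocity reduction is 20% (SD 10) with recurrence and 30% (SD 15) when stable. Two-sided alpha is 5% and power 80%. The plan needs 150 evaluable patients, 167 after 10% loss, and enrols 200.

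**Step 1: the plan's own figure.** With root-mean-square SD = sqrt((10² + 15²)/2) = 12.75 and a 1:9 split, the number of recurrent cases is

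(1 + 1/9) × (1.96 + 0.842)² × 12.75² / 10² = 14.2, rounded up to 15.

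This gives 15 + 135 = 150, and 150/0.9 = 167. The figure reproduces and is not in dispute. From 200 enrolled, 10% loss leaves 180 and about 18 events; 150 gives about 15.

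**Step 2: how often the screen drops the parameter, by crude difference.** Noncentral t, 15 v 135, two-sided 0.20. The standard error is sqrt(10²/15 + 15²/135) = 2.89 with unequal SDs, or 15 × sqrt(1/15 + 1/135) = 4.08 with a common SD of 15.

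| Crude difference (points) | Dropped, SDs 10/15 | Dropped, common SD 15 |
|---|---|---|
| 10 (planned) | 2% | 12% |
| 7.5 | 10% | 29% |
| 5 | 34% | 52% |
| 2.5 | 65% | 72% |
| 0 | 80% | 80% |

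At the planned crude difference the screen does little harm. Even a fully masked effect passes one time in five.

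**Step 3: what masking could cost.** This needs figures the document does not give, so the following are assumptions shown as a range: size OR 2 to 3 per SD, and correlation of size with flow reduction 0.3 to 0.5. The adjusted effect is set at log-OR -0.7 per SD. That is the size of the planning contrast over a weighted SD: sqrt(0.1 × 10² + 0.9 × 15²) = 14.6 and 10/14.6 = 0.69.

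Model: logit(p) = a + b × size - 0.7 × reduction, with a set for 10% recurrence, N = 180, and 3,000 simulated studies per setting.

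| Correlation | Size OR | Implied crude difference (points) | Dropped | Power if always entered with size | Power under the rule |
|---|---|---|---|---|---|
| 0.3 | 2 | 6.7 | 29% | 70% | 63% |
| 0.3 | 3 | 4.7 | 49% | 68% | 49% |
| 0.5 | 2 | 4.9 | 47% | 64% | 39% |
| 0.5 | 3 | 2.0 | 72% | 62% | 22% |

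Repeats with other random draws move these figures by up to about 3 percentage points. That is why the summary range reads about 29% to 75% dropped, with power about 61-71% falling to 20-62%.

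**Step 4: separating this from confounder selection.** The rule also screens size. If size is always kept and only the haemodynamic parameter is screened, power in the four settings is 68%, 50%, 49% and 23%. Most of the loss is therefore due to screening the exposure.

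**Step 5: other directions of confounding.** At zero correlation with size OR 2, power is 72% v 73%, no real difference. At N = 150, with adjusted log-OR -0.75 and correlation from -0.5 to 0, at most 0.4 percentage points are lost. At zero correlation the parameter still fails the screen in some studies, but almost never in one where its adjusted effect would have been significant.

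**The case against.** **The planning contrast is crude.** The 20% v 30% figures are plain group means with no adjustment mentioned, which is the quantity the screen sees. Using that contrast as the adjusted effect and then adding confounding implies crude differences of 2 to 7 points, not 10. If the crude difference is held at 10 points in the same four settings with N = 180, the parameter is dropped in only about 6% to 7% of studies. This stands. The large percentages apply only if the crude association proves much weaker than planned.

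**The direction is assumed.** The document names size and neck as risk factors and says that stents and flow diverters lower recanalisation. It does not say that large or wide-necked aneurysms receive these devices more often or have greater flow reduction. If they have less, the crude association is exaggerated and the screen keeps the parameter. This stands too. Equally, the document gives no ground for ruling masking out, and it says itself that prospective data are lacking.

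**The device route is partly blocked.** Study design plans separate analyses of conventional coiling and flow diversion. That is fair, but partial: stent-assisted coiling may remain mixed with coiling, the overall analysis is still pooled, and each subgroup has fewer events.

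**A wholly negative report is unlikely.** A reader might infer that the plan could declare no haemodynamic effect without any adjusted test. The haemodynamic section does not support that: "These parameters are wall shear stress, velocity, and pressure", with mean and maximum at two regions, makes 3 × 2 × 2 = 12 measures, plus inflow concentration. All would have to miss a lenient threshold. The risk is to a given parameter, not necessarily to the whole family.

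**Lenient screening is common in risk-factor registries.** It is, and for optional covariates it can stay. That is no reason to apply it to the exposure named in the hypothesis.

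**Conclusion.** The point holds as a conditional weakness worth correcting. The rule makes the study's exposure pass a crude test before any adjusted test, and nothing in the document exempts it.

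Its size depends on an unknown. The loss is small if the crude difference is near the planned 10 points and essentially nil at zero or negative correlation. It is substantial only in the masked settings above, which rest on an assumed correlation, an assumed size odds ratio, an adjusted effect borrowed from a crude contrast, and a single adjusting covariate.

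It would go too far to say that a real effect is discarded, or that masking is expected here. The document supports only that a masked effect can be discarded. The case for change is that entering the exposure regardless cost no meaningful power in any setting examined, and the sponsor cannot know the direction of confounding in advance.

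**What to change.** Replace the selection sentence with wording such as: *The flow velocity reduction used for the sample size enters the logistic model whatever its univariate p-value, together with a short list of covariates named in advance. Adjusted odds ratios with 95% CI for the other haemodynamic parameters are reported one at a time, including those with univariate p≥0.20, and are labelled secondary or exploratory. Univariate screening at p<0.20 applies only to optional covariates.*

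The covariate list must suit about 15 to 18 events. Aneurysm size and neck width are natural candidates, since the document names both as risk factors and records both.

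The cost is a few sentences and some extra model fits on data already planned. Two consequences should be accepted openly. Some non-significant adjusted estimates will have to be reported. About a dozen adjusted tests on so few events also bring multiplicity, which is why only the velocity reduction should carry the main conclusion.
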